## Abstract

**Abstract:**

**Introduction:**

Irritability represents one of the most common causes of referral to child and adolescent mental health services. Conceptually, tonic irritability (i.e., persistent grumpy mood) can be distinguished from phasic irritability (i.e., temper outbursts). The objective of this research project is to develop a fine-grained, ecologically valid and multimodal characterisation of tonic and phasic irritability to better understand the differential role of the two components in developmental psychopathology.

**Methods and analysis:**

The study has a longitudinal observational and experimental design and involves two sites: (a) the Division of Child and Adolescent Psychiatry at the University Hospital of Lausanne and (b) the Division of Youth Mental Health at the Faculty of Psychology at the University of Basel. 220 help-seeking and healthy youths aged 8–14 years and their families will participate in the study consisting of a baseline assessment (i.e., self-report, interviews, cognitive assessments, autonomic measures, as well as in-situ experiments), an ecological momentary assessment (EMA) phase (over 2 weeks, including experience sampling method, cognitive assessment and passive monitoring) and a 1-year follow-up. Statistical analyses will include multilevel regression (e.g., linear mixed modelling).

**Ethics and dissemination.:**

We obtained ethical approval from the local ethics committees (Cantonal Research Ethics Commission on Human Beings, CER-VD, #2023-01846) and data collection began in January 2025. The results of the present study will be published in peer-reviewed scientific journals and will be presented at key conferences in the field of child and adolescent mental health, as well as at conferences focusing on EMA. Additionally, findings will be disseminated to practitioners, the educational sector and associations working with youths. We further intend to make the findings accessible to the general public through social media, for instance.

STRENGTHS AND LIMITATIONS OF THIS STUDYThis study adopts a multimodal and multiple informants’ perspective.This study integrates a micro- (ecological momentary assessment over 14 days) and macro-longitudinal (1-year follow-up) design.Ecological momentary assessment allows for the investigation of within- and between-person variability in tonic and phasic irritability.Although this study includes physiological measures, it does not measure neuronal substrates of irritability.

## Introduction

### Irritability: a highly prevalent psychiatric symptom in childhood

 Irritability is defined as an increased proneness to anger in response to frustration compared with peers at the same developmental stage.^1 2^ For instance, children with pathological irritability have a lower threshold to express anger and therefore exhibit recurrent temper tantrums inappropriate to the situation.^3 4^ Irritability represents one of the most common causes of referral to child and adolescent mental health services.^5^,^7^ Prevalence estimates range from 20%–30% for a broad definition of irritability^5 8^ to 1%–3% for severe chronic forms of irritability.^9^,^12^ Pathological irritability is listed as a cardinal or associated symptom in many affective and behavioural disorders listed in the fith edition of the Diagnostic and Statistical Manual of Mental Disorders.^13^ Irritability is associated with long-term adverse outcomes, including low educational attainment, poor health, higher delinquency, suicidality and a higher risk for adult depression, anxiety and conduct problems.^12 8 14^,^22^ As such, irritability in childhood has been postulated to be a transdiagnostic marker of psychopathology crossing externalising and internalising dimensions.^2123^,^28^

### Two components of irritability

Previous studies mainly characterised irritability as a unitary clinical phenomenon, resulting in a poor definition of irritability and a lack of a clear understanding of its clinical correlates and pathophysiology. Most recent conceptualisations distinguish tonic from phasic irritability.^29^,^32^ While tonic irritability refers to a persistently angry, grumpy, bad-tempered or grouchy mood, usually lasting days and weeks, phasic irritability refers to behavioural outbursts of intense anger, manifested by brief or protracted verbal or physical aggression.^30 33 34^ The clinical distinction, as well as the boundaries between tonic and phasic irritability, is highly correlated; however, they are distinguishable^35 36^ already at 3 years of age.^37^ Further, recent studies showed that, in adolescence, the two components of irritability showed distinct concurrent correlates and early antecedents^38^ and distinct patterns of development and co-development, suggesting discriminant validity^39^ that may also be identified by parents and teachers.^40^

The distinction between phasic and tonic irritability has emerged in the context of investigations focused on disruptive mood dysregulation disorder (DMDD), a diagnostic category recently introduced in psychiatric diagnostic manuals and characterised by the presence of both components.^31 41^

### Clinical correlates of tonic and phasic irritability

While tonic irritability seems to be more closely related to internalising psychopathology, phasic irritability has stronger links to externalising psychopathology.^35^ Indeed, in cross-sectional studies of help-seeking children between the ages of 5 and 18, phasic irritability was associated with attention-deficit/hyperactivity disorder (ADHD) symptoms^42^ and externalising problems but not internalising symptoms.^43^ Longitudinal studies in community children reported that tonic irritability predicted subsequent depression and generalised anxiety disorder, while phasic irritability was slightly more stable, rather heritable and more frequently predicted later ADHD, oppositional defiant disorder, conduct disorder and substance use disorder.^35 44^ The distinction between tonic and phasic irritability even allows for the distinction between symptom constellations in depression and suicidality.^45 46^ In another longitudinal study of a community sample of 13–22year-olds, tonic irritability predicted ADHD at age 16 and major depressive disorders at age 22, whereas phasic irritability predicted phobias and hypo-/mania at age 16.^29^ Nevertheless, in a longitudinal study of a community sample of 9–13-year-olds, tonic and phasic irritability predicted similar outcomes, while phasic irritability was more prevalent than tonic irritability.^33^ Regarding the mixed results observed in previous studies, further research is needed.

### Dynamics of irritability at the within-person level

Although irritability is omnipresent in distinct psychiatric disorders, its manifestation is highly heterogeneous across and within individuals. The reason for this might—at least in part—lie in its two components, which differentiate in their temporal dynamics. While tonic irritability persists for days, phasic irritability typically lasts for minutes to a couple of hours. The important question of whether tonic and phasic irritability are independent events or whether mood between tantrums is a series of less severe outbursts^34 47^ could be approached by using ecological momentary assessment (EMA). EMA includes the so-called experience sampling method (ESM), which consists of frequent, repeated self-report assessment of thoughts, cognition, experiences and behaviours^48 49^ via a handheld device—usually a smartphone.^50^ Moreover, EMA includes passive monitoring (e.g., actigraphy, monitoring of smartphone use), physiological measures, as well as cognitive EMA.

EMA has high ecological validity compared with traditional clinical diagnostics. Patient’s reports do not suffer from recall bias due to long-term retrospective assessment, which may be advantageous, as studies suggest that irritable youth may under-report levels of symptoms, retrospectively, in comparison to their peers.^24 51^ To date, irritability has been examined using parent or clinician ratings to examine irritability without distinguishing tonic and phasic dimensions, mainly at the between-person level. One notable exception is a very recent transdiagnostic study using ESM to examine pathological irritability and demonstrated the feasibility and reliability of measuring this symptom in 109 children and adolescents aged between 8 and 18 years.^52^ The authors observed convergent validity of ESM measures of irritability with clinical self-report and interview measures, as well as with a task inducing mild levels of frustration,^53 54^ namely the Stop Signal task (SST).^55^ Even though the authors assessed both components of irritability, they did not distinguish between the two components in their analyses. Thus, further studies are needed to refine the tonic-phasic distinction using EMA, including not only experience sampling but other modalities (e.g., cognitive or autonomic function).

### Time-course approach to cognitive and autonomic underpinnings of irritability

The cognitive and neurobiological pathways leading to pathological irritability have been hypothesised to be grounded in deficits in instrumental learning, which enable children to adapt their behaviour to respond most appropriately to environmental stimuli.^2^ In typical development, emotion regulation skills develop in response to frustration during the preschool period.^56 57^ While anger is a normative response to frustrative non-reward, the chronic negative affective response to non-reward might stem from a deficit in emotion regulation and eventually lead to pathological irritability. A key construct of emotion regulation is cognitive control (or inhibitory control), which has been posited as a crucial mechanism that may affect the generation and maintenance of irritability^2 58^ but has not been extensively investigated in this context yet.

Children with conduct disorders, autism and ADHD showed higher emotional responses alongside a lower autonomic regulation pattern (i.e., higher sympathetic arousal) in response to frustration.^659^,^62^ However, autonomic markers of emotion dysregulation have not been extensively studied in the context of irritability yet.^63 64^ The pattern of respiratory sinus arrhythmia (RSA: influence of respiration on heart rate) changes in response to frustration induction was related to better emotion regulation and adjustment (i.e., more prosocial behaviours) in community adolescents.^65^ Moreover, the duration of RSA recovery after emotion induction was found to be crucial in the distinction between functional and dysfunctional emotion regulation,^66 67^ highlighting the importance of assessing detailed time-courses of patients’ emotion reactivity in challenging situations.^68 69^ Such time courses can be measured using the ‘in-situ’ approach, which might reveal non-linear associations of dysfunctional psychophysiological processes in irritability.^70^ Preliminary findings showed that irritability is related to increased heart rate and decreased heart rate variability (HRV) during the performance of an SST, inducing mild frustration, in a transdiagnostic sample (n=51) presenting with irritability (i.e., ADHD, DMDD, anxiety disorders vs healthy controls).^53 54 71^ ‘In-situ’ studies inducing higher levels of frustration in children with irritability are, thus, warranted.

### Psychosocial environment

Further, the psychosocial environment and, in particular, the interpersonal dynamics of caregiver-child interactions may be of importance to understand irritability.^72^ Indeed, phasic irritability was uniquely related to self-reported maladaptive parenting.^36^ During development, parent–child interactions evolve to meet the needs of the child, resulting in many adjustments for both the parent (i.e., co-regulating their child’s emotions^73^) and the growing child,^74^ including irritability.^75 76^ Thus, the quality of parenting is important for the child’s self-regulation,^73 77^ as are the parent’s own self-regulatory resources to help the child develop adaptive anger management skills.

### Research gaps

A central question is whether tonic and phasic irritability reflect different intensity levels along a single continuum or constitute related but distinct phenotypes.^34^ This study uses ecologically valid, multimodal and multi-informant assessments, as well as EMA, to characterise both dimensions. By integrating cognitive, psychosocial, psychophysiological and autonomic measures, the study aims to clarify within-person dynamics and identify proximal markers of tonic and phasic irritability. This approach will also allow for the examination of their concurrent and longitudinal associations with clinical outcomes, with the goal of laying a foundation for future work improving early identification and intervention targets.

### The current research project

The overall objective of this research project is to develop a fine-grained, ecologically valid and multimodal characterisation of tonic and phasic irritability in order to better understand the differential role of the two components of irritability in developmental psychopathology. In particular, through ESM assessment, our *first aim* is to validate the tonic—phasic distinction of irritability at the within-person level and to determine the temporal dynamics as well as the natural context of expression of the two components. We hypothesise that the tonic and phasic components of irritability measured with ESM will be strongly and consistently associated with their respective well-established clinical measures, thereby providing new, reliable and complementary measures. We further assume that high levels of tonic irritability will precede phasic irritability (i.e., temper tantrum). Moreover, contextual information (including parenting) about the current psychosocial environment might be differently related to tonic vs phasic irritability.

Our *second aim* is to examine whether distinct cognitive and autonomic correlates of tonic and phasic irritability exist, both at the within-person level and at the between-person level. Related to this aim, we hypothesise that experimental measures of ambulatory cognitive control will be more strongly associated with phasic than tonic irritability. From the ‘in-situ’ assessment, we expect that HRV reactivity will be more specifically related to phasic aspects of irritability (clinical and ESM assessments), whereas HRV recovery (more related to emotion regulation) will be associated with tonic irritability (ESM and well-established clinical assessments). Finally, by means of the autonomic EMA, we expect to identify autonomic dysregulation concurrent with tonic irritability but probably preceding episodes of phasic irritability.

## Methods and analysis

This research project employs a longitudinal design combining observational and experimental elements. The project is a multi-centre study including two sites: (a) the Division of Child and Adolescent Psychiatry at the University Hospital of Lausanne and (b) the Division of Youth Mental Health at the Faculty of Psychology at the University of Basel. The data collection phase begins in January 2025 and will last until the end of 2027.

### Participants

We will recruit n=180 youths who are currently seeking help from various child and adolescent mental health services (as well as those who have sought help in the past 12 months). Moreover, we will recruit n=40 healthy children (i.e., not seeking help and no diagnosed psychiatric disorder). In addition, we will recruit participants’ parents (n=220–440). Thus, the total sample of the study will range from 440 to 660. Table 1 describes the inclusion and exclusion criteria. The sample size of a total of n=220 children was justified by a power calculation (see power calculation section).

**Table 1 T1:** Inclusion/exclusion criteria for children and their legal guardians

Criteria	Children	Legal guardian
Inclusion		
Being aged 8–14 years	x	
Having sufficient intellectual abilities and sufficient language skills (German or French) to be able to participate in the study	x	x
Drug naïve (no psychotropic medication, no medication impacting heart rate)*	x	
Written informed assent or written informed consent	x	x
Exclusion		
Known cardiovascular disorders impacting the heart functioning, severe health conditions that currently demand intensive medical treatment (i.e., cancer, neurological disease, severe conditions related to mental health)	x	
Having a pacemaker	x	
Known diagnoses in schizophrenia or psychosis spectrum as well as in autism spectrum disorders at study inclusion	x	
Known active life crisis (i.e., intense suicidal ideas or behaviours)	x	

* As we aim to characterise the associations between these phenomena without the confounding influence of medication that may alter emotional, behavioural and psychophysiological functioning.

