### Statistical analysis plan

We will assess cross-language measurement invariance (French vs German) for multi-item scales using multi-group confirmatory factor analysis, testing configural, metric and scalar (threshold) invariance based on model fit and Δcomparative fit index (CFI)/Δroot mean square error of approximation (RMSEA). If inter-site differences are detected, the site will be included as a covariate in the statistical models to control for potential confounding.

#### Aim 1

First, we will compute separate standardised composite scores for tonic and phasic irritability at the within- (from the ESM measures) and between-person level (from the interviews and questionnaires). To assess convergent validity, multilevel regression models will then be used to test for associations between the tonic irritability composite score from ESM measures and the tonic irritability composite score from the clinical measures. The same models will be computed for phasic irritability. To test our second hypothesis, we will compute a lagged logistic multilevel regression model where tonic irritability from one ESM sampling will predict the presence of phasic irritability (categorical score) in the next ESM sampling (within-person level). Finally, to investigate the role of the psychosocial context (including parenting), multilevel regression analyses will be used to assess the role of conflict and psychosocial context on tonic/phasic irritability at the within-person level.

#### Aim 2

To test the pathophysiological correlates of tonic and phasic irritability, we will compute a multivariate linear mixed model,^115^ which represents a statistical framework for analysing fixed and random effects on multiple outcomes (i.e., tonic vs phasic irritability).^116^ This approach enables us to compare the effects of the pathophysiological variables on tonic versus phasic irritability, which are two separate but correlated outcomes. The model will hence allow computing effect sizes that will be compared with assessing the common and unique pathophysiological correlates (i.e., ambulatory cognitive control, ‘in-situ’ HRV) of tonic and phasic irritability both at a within- and between-person level. Lagged multilevel regression models will further be used to assess the temporal dynamics of the pathophysiological (e.g., ambulatory HRV, actigraphy and cognitive control) correlates of tonic and phasic irritability at the within-person level.

#### Aim 3

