Finally, to understand the role of tonic and phasic irritability in psychopathology, two approaches will be used. First, we will adopt a dimensional perspective and use the severity of psychopathology of internalising and externalising problems (as the outcome variables at the between-person level). We, thus, must reduce the ESM measures to single measures for each participant. To do so, we will compute the mean and RMSSD that will be used in hierarchical regression analyses, also including the measure of irritability from clinical (or baseline) assessment. As both dimensions of irritability will be correlated and thus share a great part of common variance, we will compute the unstandardised residuals from regression analyses (tonic irritability regressed on phasic irritability and conversely).^117^ These scores will be used in the following regression models in order to calculate the independent importance of one dimension of irritability in understanding the severity of psychopathology. Second, we will adopt a transdiagnostic approach and use multilevel regression analyses (i.e., means-as-outcomes models)^118^ as proposed in the only previous paper combining within- and between-person approaches^51^ to assess the differences in ambulatory tonic and phasic irritability (within-person level) across diagnoses (between-person; e.g., anxiety, depression, DMDD, ADHD and oppositional defiant disorder).

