#### Power analyses

We approximated the power of the main analyses (i.e., the multilevel regression) by using Monte-Carlo simulation (n=1000 repetitions). Based on pilot studies (unpublished data), we assumed a correlation coefficient of r=0.75 between repeated measures, participant compliance of 82% and an additional dropout of 20%. For the concurrent model, 56 repeated measures for each participant (4× measure a day for 14 days) will be collected for n=220 participants. For the temporal model (or lagged model, predicting next measures), 42 measures (three lagged variables per day for 14 days) will be available for the 220 participants. We expect a correlation between tonic and phasic irritability of r=0.60.^35^ The approximated power of these analyses focuses on the effects of β_n_ (between-person level) and γ_n_ (within-person level) for the repeated measures. These models have a power of 0.99 to detect small effect sizes at the within-person level and a power of 0.94 to detect medium effect sizes at the between-person level. For the temporal model (lagged model), we will achieve a power of 0.91 to detect small effect sizes at the within-person level and a power of 0.82 to detect medium effect sizes at the between-person level.

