In line with the most recent view of psychiatric disorders as continuous and dimensional phenomena rather than clearly delineated categorical entities, the proposed project thus takes a dimensional approach to quantification and severity of psychiatric symptomatology, abandoning the purely categorical diagnostic approach. Moreover, the naturalistic approach, including the parental perspective as well as using passive smartphone sensing, our project will lead to a better understanding of the contextual and interpersonal factors associated with irritability. Most importantly, our study is more likely to give insights into the psychophysiology of psychiatric disorders than approaches which examine disorders in a categorical manner.^123 124^ The proposed project, therefore, leverages the full spectrum of irritability in the help-seeking clinical sample and healthy control sample in combination with state-of-the-art clinical, cognitive, psychophysiological and neurobiological assessments, to contribute to the limited understanding of the underlying mechanisms of tonic and phasic irritability. Clinical re-evaluation of study participants will further allow us to determine the predictive value of tonic and phasic irritability for current and future psychopathology. The proposed project might further constitute the basis of a future cohort study. There is great potential in following these children up into adolescence and adulthood to understand the developmental pathways related to tonic and phasic irritability and its later consequences. A cohort study would further help to identify the best targets for early personalised intervention, reducing the negative long-term outcomes.

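### Between-person associations pool 180 help-seekers with 40 children selected for having no diagnosed disorder, and the stated models carry no recruitment-group term, so a group gap can be reported as a dimensional association

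*Protocol article*

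**What the plan says.** The Participants section sets two recruitment rules. For the larger group: "We will recruit n=180 youths who are currently seeking help from various child and adolescent mental health services" (or did so in the past 12 months). For the smaller group: "Moreover, we will recruit n=40 healthy children (i.e., not seeking help and no diagnosed psychiatric disorder").

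The Power analyses section treats them as one sample: "56 repeated measures for each participant (4× measure a day for 14 days) will be collected for n=220 participants". The Scientific relevance section shows that pooling is deliberate, since the project "leverages the full spectrum of irritability in the help-seeking clinical sample and healthy control sample".

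The Statistical analysis plan section names one grouping variable as a possible covariate: "If inter-site differences are detected, the site will be included as a covariate in the statistical models to control for potential confounding". It mentions no recruitment-group term and no estimate within help-seekers, and it gives the healthy children no separate role.

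For the dimensional part of Aim 3 the plan will "use the severity of psychopathology of internalising and externalising problems (as the outcome variables at the between-person level"). Because tonic and phasic scores are correlated, "we will compute the unstandardised residuals from regression analyses (tonic irritability regressed on phasic irritability and conversely"). A second Aim 3 approach compares ambulatory irritability across diagnoses.

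**The concern.** The healthy children are selected on something close to the Aim 3 outcome: they have no diagnosed disorder. The protocol's introduction describes irritability as a common reason for referral, so help-seekers can be expected to score higher on irritability and on psychopathology together. When two groups differ on both variables, the pooled between-person slope combines the association inside each group with the line joining the two group means. Two measures unrelated among help-seekers can then look related.

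The hypotheses are about dimensional differences in irritability. That referred children differ from children without a diagnosis is a different and less informative finding. The pooled coefficient also depends on the recruitment quota. With a 1.5 SD gap on both measures and no association within groups, the 40:180 split gives r = 0.25, while a 50:50 split would give 0.5625/1.5625 = 0.36.

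Three places are exposed: the Aim 1 regression of ESM composites on clinical composites, the between-person part of the Aim 2 multivariate model, and the Aim 3 hierarchical regressions.

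**Working it through.** **Inputs from the protocol.** Help-seeking 180, healthy 40, total 220 (Participants). Dropout 20% and expected tonic-phasic correlation 0.60 (Power analyses). After dropout: 220 × 0.8 = 176, that is 144 + 32.

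**Assumptions.** The group gap d in SD units (the protocol gives none), unit SD within groups, two-sided alpha 0.05.

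**The plan's own figure.** The protocol states between-person power of 0.94 for a medium effect in the concurrent model. It gives no numerical effect size or alpha, so the figure cannot be uniquely reproduced. A standardised slope of 0.30 with a predictor correlation of 0.60 gives 0.945 at n = 220; r = 0.30 gives 0.946 at n = 136. The figure is not disputed here.

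**Step 1: correlation induced by pooling.** Healthy share p = 40/220 = 0.182, so p(1−p) = 0.149. With within-group correlation w and the same gap d on both measures:

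pooled r = (w + 0.149 d²) / (1 + 0.149 d²)

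With w = 0, for example at d = 1.5: 0.149 × 2.25 = 0.335, and 0.335/1.335 = 0.25. The chance of p < 0.05 uses Fisher's z: Φ(atanh(r) × √(n−3) − 1.96). At d = 1.0 and n = 220 this is Φ(0.130 × 14.73 − 1.96) = Φ(−0.04) = 0.48.

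| Gap on both (SD) | Pooled r | p < 0.05, n = 220 | p < 0.05, n = 176 |
|---|---|---|---|
| 0.5 | 0.04 | 8% | 7% |
| 0.8 | 0.09 | 25% | 21% |
| 1.0 | 0.13 | 48% | 40% |
| 1.5 | 0.25 | 97% | 92% |

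Simulation of the same regression agrees: 42% (n = 176) and 49% (n = 220) at 1.0 SD; 94% and 97% at 1.5 SD.

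A true association is inflated in the same way. A within-group r of 0.30 is read as 0.39 at d = 1.0 and 0.48 at d = 1.5.

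**Step 2: the Aim 3 residualised scores.** Simulation with a within-group tonic-phasic correlation of 0.60, an outcome unrelated to both within groups, and no group term (1,500 runs per scenario). Each cell gives n = 176, then n = 220.

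| Gap: tonic / phasic / outcome (SD) | Tonic residual p < 0.05 | Phasic residual p < 0.05 |
|---|---|---|
| 0.5 / 0.5 / 0.5 | 6%, 5% | 5%, 6% |
| 1.0 / 1.0 / 1.0 | 13%, 14% | 12%, 14% |
| 1.5 / 1.5 / 1.5 | 30%, 34% | 28%, 34% |
| 1.5 / 1.0 / 1.5 | 65%, 74% | 5%, 5% |
| 1.5 / 0.8 / 1.5 | 80%, 88% | 5%, 5% |
| 0.8 / 1.5 / 1.5 | 5%, 5% | 77%, 85% |

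Equal gaps inflate both residuals alike. Only unequal gaps give a one-sided pattern, which then favours the component with the larger gap.

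**Step 3: with a group term.** In the same scenarios (800 runs each), rejection returns to about 4-7% for the zero-order and the residualised scores.

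**Step 4: what is not exposed.** The Aim 1 lagged and context models and the Aim 2 lagged models are stated at the within-person level. A stable group difference does not enter such effects when predictors are centred within person. The second Aim 3 approach already has diagnosis as its between-person predictor.

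**The case against.** **The article is condensed.** Covariate lists are often left to a fuller document, and nothing here says that group will be left out. Age and sex are not listed as covariates either. This stands as a caution: the omission is read from silence. But the article does fix the pooling, the N of 220 and a covariate rule for site, so an analyst following it as written would fit the pooled model.

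**Pooling has a rationale.** The protocol deliberately takes a dimensional view, and a wide range is useful for that. For Aim 1, ESM and clinical scores that both separate the groups are some evidence of validity. This stands, and it is why the pooled estimate should be kept. It does not show that the slope within groups equals the slope between them.

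**The gap may be small.** Healthy children are not selected for low irritability, help-seekers are not selected for high irritability, and known active crisis and severe conditions are excluded. For HRV a large gap is less plausible. With 1.0 SD on irritability and an assumed 0.3 SD on HRV, r = 0.149 × 1.0 × 0.3 / √(1.149 × 1.013) = 0.04, significant in about 9% of studies at n = 220. This stands as a limit on size.

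**Adjustment can mislead too.** Group is partly defined by psychopathology, so a group term may over-adjust in Aim 3, and restriction to help-seekers narrows the range. This stands against making either one the sole analysis.

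**A stronger reading.** A reader might infer that the group gap by itself would produce the predicted tonic-internalising and phasic-externalising pattern. The documents do not support that. Equal gaps raise both components together, residualisation weakens the effect, and no passage says that the tonic and phasic gaps differ.

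**Conclusion.** The point holds for three sets of between-person analyses: Aim 1 convergence, Aim 2 between-person correlates and the Aim 3 dimensional regressions. As written, they can report a difference between recruitment groups as a dimensional association.

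The size depends on gaps that the protocol does not give. It is substantial for simple associations if the groups differ by about 1 SD or more on both measures, clearly smaller for the residualised scores under equal gaps, and negligible near 0.5 SD. A spurious tonic-versus-phasic contrast is possible only under the further assumption of unequal gaps.

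A reader might also conclude that every between-person model is compromised, or that only an association that survives within help-seekers should count. Neither follows: the diagnosis-based model carries its own group-type predictor, and the help-seeking-only slope has selection and range problems of its own.

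**What to change.** In the preregistration, which the protocol plans before the analyses are run, state for each between-person hypothesis in Aims 1 to 3 that three estimates will be reported side by side:

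1. the pooled full-spectrum estimate, as now planned;
2. the same model with recruitment group (help-seeking or healthy) as a term;
3. the estimate in the 180 help-seekers alone.

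State how they will be read. An association is described as dimensional with reference to whether the three agree. Where they disagree, it is reported as partly or wholly a group difference. The within-person models and the diagnosis-based Aim 3 model need no change.

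Cost: a few extra models on data already being collected, with no change to recruitment. The help-seeking-only estimate covers a narrower range and is less precise: on the Fisher z scale its standard error is larger by √(217/177) = 1.11, about 11%. The group-adjusted estimate may over-adjust in Aim 3. For these reasons the pooled estimate stays and no single estimate decides whether a claim may be made.
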